#### 2.6.3. Integration of Quantitative and Qualitative Findings

Firstly, quantitative and qualitative data will be analyzed independently, following their respective methodologies. Subsequently, the findings will be integrated to address the study’s objectives and hypotheses, providing a more comprehensive understanding of the intervention and its scope.

#### 2.6.4. Data Monitoring

The study will be overseen by the research team, which will verify protocol compliance, data confidentiality, and information safeguarding. Periodic internal meetings will be held to review progress, safety, and protocol adherence.

### 2.7. Expected Primary and Secondary Outcomes

The outcome variables are defined in the following subsections.

#### 2.7.1. Primary Outcomes

Healthy lifestyle (well-being): Behaviors related to nutrition, physical activity, and other healthy habits will be assessed as indicators of well-being.Burnout (ill-being): Physical and emotional exhaustion, sense of accomplishment, and devaluation of sports practice will be evaluated as indicators of ill-being.The variable of interest in both cases will be the change after the intervention, calculated as the difference between post-intervention and baseline scores.

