#### 2.2.4. Sample Size and Randomization

The study will employ a non-probabilistic convenience sampling [44], including participants who meet the established inclusion criteria and are available during the recruitment period.

The sample size (*n* = 80) was determined pragmatically and based on operational feasibility, considering the resources and organizational requirements of the intervention, including the facilitators’ capacity, the availability of staff responsible for implementation, the total program duration, and the estimated recruitment period.

The participants will be distributed equally between the two intervention modalities, with 40 participants per modality (20 men and 20 women in each; see Table 1).

Randomization will be conducted using a computer-generated procedure, applying stratification to ensure an equitable distribution between the groups. The randomization will be generated and safeguarded by a researcher independent of the intervention. Once the assignment is generated, each participant will be notified individually.

Blinding of the participants and facilitators is not feasible due to the nature of the intervention delivery format. The face-to-face and semi face-to-face modalities differ in observable aspects, such as the type of interaction, communication channels, and module dynamics, making it impossible to conceal the assigned modality. Nevertheless, participants will not receive information regarding the activities or specific structure of the alternative modality. Likewise, facilitators will necessarily be aware of the format of the modality they deliver.

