#### 2.3.3. Assessment Timeline

Evaluations will be conducted at the following times:Time 1. Week 0: What is My Lifestyle Like? Survey.Time 1. Week 2: Controlling Coach Behaviors Scale, Perceived Autonomy in Sport Scale, Perceived Competence Scale, Need for Relatedness Scale, Sport Motivation Scale II, and Athlete Burnout Questionnaire. The questionnaires will be administered at this point because they will assess the variables that require the participants to have previously interacted with the program components in order to be appropriately perceived.Time 2. Week 13: All instruments and the focus group will be administered.

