### 2.6. Data Analysis

#### 2.6.1. Quantitative Analysis

Due to the practical limitations in following up with those participants who do not complete the program, the primary analysis will be conducted using a per-protocol approach [111], considering only those participants with complete data at baseline and at the end of the intervention; missing data will not be imputed.

This approach will allow for evaluating the changes associated with each intervention under real-world implementation conditions, acknowledging the anticipated risk of participant attrition and that the benefits of randomization may not be fully preserved, while reflecting its applicability in a pragmatic context.

All statistical analyses will consider a 95% confidence level (5% error), ensuring transparency and reproducibility.

Preliminary Analysis. Descriptive statistics for central tendency (mean, median), dispersion (standard deviation and variance), and distribution (skewness and kurtosis) will be estimated for each observed variable. Next, normality tests will be conducted, and the reliability of the instruments will be estimated by measuring their internal consistency through Cronbach’s alpha (α) and McDonald’s omega (ω) coefficients. Subsequently, bivariate correlation analyses will be performed to measure the strength and direction of the relationship between the variables.

Associations among motivational and outcome variables. To examine the associations between the coach’s controlling interpersonal style, basic psychological need satisfaction, autonomous motivation, healthy lifestyle, and burnout, hierarchical multiple regression analyses will be conducted. Separate models will be estimated for each intervention modality (face-to-face and semi face-to-face) and for each measurement occasion (baseline and post-intervention), with predictor variables entered in a theoretically driven manner [42]. Effect sizes and confidence intervals will be calculated to complement the statistical significance, and statistical power will be considered when interpreting the results [112].

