Intervention-related changes. Changes in the coach’s controlling interpersonal style, basic psychological need satisfaction, autonomous motivation, healthy lifestyle, and burnout from baseline to post-intervention will be examined. Within-group pre-post comparisons will be conducted for each intervention modality (face-to-face and semi-face-to-face). Between-group comparisons will assess whether the magnitude of changes differs between the two modalities [42]. Effect sizes will be calculated to quantify the magnitude of the observed changes, and statistical power will be considered in interpreting the results [113].

Mediation effects. The effects of basic psychological needs satisfaction and autonomous motivation as mediating variables (the mediation effect of basic psychological needs satisfaction and autonomous motivation on the relationship between the coach’s controlling interpersonal style, healthy lifestyle, and burnout, as well as the effect of basic psychological needs satisfaction on the relationship between autonomous motivation, healthy lifestyle, and burnout) will be evaluated using regression-based mediation analyses with bootstrapping procedures to estimate direct and indirect effects following Hayes’s recommendations [43], considering pre- and post-intervention data. The significance of mediation inferred when the confidence interval of the indirect effect does not include zero allows for the assessment of whether the observed relationships are explained directly or indirectly through the proposed mediating variables. Mediation effects will be considered exploratory due to the sample size and the nature of the study.

Moderation Effects. The moderating effects of both intervention modalities will be evaluated using regression-based moderation analyses, following Hayes’s recommendations [43], considering both pre- and post-intervention data. Moderation will be examined by including interaction effects, as evaluated through bootstrapped confidence intervals. Significant interaction effects will indicate that the strength or direction of the relationship between predictors and outcomes differs according to the intervention modality. Moderation effects will be considered exploratory due to the sample size and the nature of the study.

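### For healthy lifestyle, the modality comparison rests on change from baseline with no stated adjustment for the week-0 score or the stratification factor, which gives up precision

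*Protocol article*

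**What the plan says.** Section 2.7.1 names healthy lifestyle and burnout as the primary outcomes and fixes the metric for both: "The variable of interest in both cases will be the change after the intervention, calculated as the difference between post-intervention and baseline scores". In section 2.6.1, the paragraph on intervention-related changes plans pre-post comparisons within each modality and adds: "Between-group comparisons will assess whether the magnitude of changes differs between the two modalities". It names no model and no covariate for that between-modality comparison. For the other quantitative objectives the same section does name a method: hierarchical regression for associations, and regression with bootstrapping for mediation and moderation.

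Section 2.2.4 says allocation is computer-generated, "applying stratification to ensure an equitable distribution between the groups". It does not name the factor. It does give 40 participants per modality, 20 men and 20 women in each, which points to sex. The total of 80 "was determined pragmatically and based on operational feasibility", with no effect size, standard deviation, power or pre-post correlation.

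Section 2.3.3 and Table 1 place the lifestyle survey at week 0 ("Time 1. Week 0: What is My Lifestyle Like? Survey"). The burnout questionnaire (ABQ) is first given at week 2, because it is among the measures said to "require the participants to have previously interacted with the program components in order to be appropriately perceived". Both modalities start in week 1.

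**The concern.** Taken at face value, the stated metric leads to a two-group contrast of change scores. Such a contrast forces the slope of follow-up on baseline to equal 1. When the true slope is smaller, which is the usual case for a questionnaire score repeated after three months, part of the noise in the baseline measurement is carried into the outcome. A chance difference between the groups at baseline is then subtracted in full, although only a fraction r of it would persist to week 13.

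Precision is scarce here. The sample was set by feasibility, there are at most 40 per arm, and only participants with complete data are analysed. The week-0 lifestyle score and sex are collected anyway, so the loss is avoidable at no cost in data. Naming the adjustment in advance also removes a later choice between adjusted and unadjusted results.

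**Working it through.** **Inputs from the protocol.** 40 per modality (2.2.4); 5% error (2.6.1), taken as two-sided because sidedness is not stated; lifestyle at weeks 0 and 13 (2.3.3). The sample size has no statistical basis, so there is no planned power figure to reproduce.

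**Assumptions.** The pre-post correlation r is not given; 0.3 to 0.8 is shown. The score is assumed to have the same SD, σ, at both times. Attrition is expected but not quantified; 20% is used as an illustration, leaving 32 per arm.

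**Variance per participant.**
- Change score: 2(1−r)σ².
- Adjusted for baseline: (1−r²)σ².
- Ratio, adjusted to change: (1−r²) / [2(1−r)] = (1+r)/2.

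The ratio is below 1 for every r below 1. When r is below 0.5, 2(1−r) exceeds 1, so subtracting the baseline is then less precise than ignoring it.

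**Detectable difference.** For an outcome with SD 1, 40 per arm, two-sided 5% and 80% power, the noncentral t gives 0.634 (the normal approximation gives 0.626). Multiply by √[2(1−r)] for change and by √(1−r²) for the adjusted analysis. At r = 0.5: 0.634 × √1.00 = 0.634 and 0.634 × √0.75 = 0.549.

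| r | Variance ratio | Detectable difference (SD), change vs adjusted | Power for 0.5 SD, 40 per arm | Power for 0.5 SD, 32 per arm |
|---|---|---|---|---|
| 0.3 | 0.65 | 0.75 vs 0.61 | 47% vs 65% | 39% vs 55% |
| 0.5 | 0.75 | 0.63 vs 0.55 | 61% vs 73% | 52% vs 64% |
| 0.7 | 0.85 | 0.49 vs 0.45 | 82% vs 88% | 73% vs 80% |
| 0.8 | 0.90 | 0.40 vs 0.38 | 94% vs 96% | 89% vs 92% |

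The powers use the normal approximation. In sample-size terms, 1/0.65 = 1.54, 1/0.75 = 1.33 and 1/0.85 = 1.18, so the change-score contrast needs 54%, 33% or 18% more participants for the same precision.

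**Chance imbalance.** One standard error of the baseline difference at 40 per arm is √(2/40) = 0.22 SD. Given a baseline difference Δ, the change contrast is expected to miss the true effect by rΔ − Δ = −(1−r)Δ. For Δ = 0.22 SD this is −0.16, −0.11, −0.07 and −0.04 SD at r = 0.3, 0.5, 0.7 and 0.8. Averaged over randomisation, Δ is zero and so is the bias.

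**Stratification factor.** A simulation (4,000 runs per setting, 40 per arm, r = 0.5, sex balanced within arm, true effect 0.5 SD) compared baseline adjustment without and with sex. Power went from 72% to 72% if sex has no effect on the week-13 score, 69% to 72% if its effect is 0.5 SD, and 65% to 72% if it is 0.8 SD. When sex mattered, leaving it out gave a type I error of about 4%, which is slightly conservative.

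**Equivalence.** Subtracting the baseline B from both sides of Y = a + τ·modality + b·B gives Y − B = a + τ·modality + (b−1)·B. The modality coefficient τ is the same, so adjusting the change for week-0 score gives the same answer as adjusting the week-13 score.

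**The case against.** The strongest reply is that the protocol does not specify an unadjusted comparison. It defines a metric and names no model, covariates are often left to an analysis plan, and a change score can be analysed with baseline as covariate. This stands in part. A reader might infer that the plan deliberately ignores baseline and the sex strata; the text does not say so, and it does not name sex as the stratification factor. The point survives in narrower form: the primary metric is fixed, methods are named for the other quantitative objectives, and the stated comparison followed as written yields the less precise contrast.

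A reader might also infer that baseline imbalance goes uncorrected, or that the contrast is biased. Neither follows. Change scores over-correct imbalance, and before attrition the contrast is unbiased over randomisation.

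Change is also the natural measure for the leading part of Hypothesis 2, which expects pre-post change within modalities in a trial without an untreated group. That stands, and change should remain the measure there.

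Finally, the size depends on an r that the document does not supply, and the gain is small at 0.8 or above. That stands too.

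**Conclusion.** The point holds for the between-modality comparison of healthy lifestyle. It concerns efficiency, not validity. Adjusting for the week-0 score lowers the variance by 35% to 10% as r goes from 0.3 to 0.8. At r = 0.5 and 40 per arm the detectable difference improves from about 0.63 to 0.55 SD. These figures assume the stated range of r and equal SDs at both times. The stratification factor adds a modest gain of 0 to 7 power points, depending on how prognostic sex is.

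It is tempting to apply the same figures and remedy to burnout, but the documents do not support that. The first ABQ score is taken at week 2, after both modalities have started, so it may already carry a modality effect. Adjusting for it could remove part of the effect of interest, as subtracting it could.

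Adjustment does not repair the complete-case analysis. Section 2.6.1 itself concedes that randomisation may not be fully preserved among completers; a baseline term deals only with imbalance in the measured score.

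**What to change.** State in sections 2.6.1 and 2.7.1 that the between-modality effect on healthy lifestyle is estimated from a linear model of the week-13 score (or, equivalently, the change) on modality, week-0 lifestyle score and the randomisation stratification factor(s), reported as an adjusted mean difference with a 95% CI. Name the factor(s) in section 2.2.4; sex appears to be one.

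Keep pre-post change for the within-modality comparisons. For burnout, include the stratification factor in the between-modality comparison, and do not rest a baseline-adjustment argument on the week-2 score.

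The cost is a sentence or two of text, with no new data, visits or participants.

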#### 2.7.2. Secondary Outcomes

Basic psychological needs satisfaction: Changes in autonomy, competence, and relatedness will be evaluated as potential mediators of the intervention’s effects.Autonomous motivation: Autonomous motivation, composed of intrinsic, identified, and integrated regulation, will be evaluated as a mechanism mediating the effects of the intervention on healthy lifestyle and burnout.Controlling interpersonal coaching style: The perception of control and pressure exerted by the coach, including task imposition and reward manipulation, will be assessed as a contextual predictor to understand its influence on the intervention effect sequence.

The metric for all secondary outcomes will be the change in total post-intervention scores relative to baseline.

#### 2.7.3. Acceptability and Perceived Contribution

Intervention acceptability: The participants’ perception of the PsicoFIT structure, content, and methodology will be evaluated, identifying positively valued aspects and areas requiring adjustments.Perceived contribution: The participants’ perceptions of the intervention’s impact on their motivation toward physical activity, adoption of healthy habits, well-being, and management of ill-being will be explored.

This information will complement the quantitative results, providing qualitative evidence on how the participants value the intervention and perceive its contribution to achieving well-being and healthy habits.

### 2.8. Ethical Considerations

This study is part of the protocol titled: “*Programa Integral de Bienestar Incomparables TIGREFIT para población sedentaria y con sobrepeso*” (Comprehensive Unparalleled Well-being Program TIGREFIT for Sedentary and Overweight Population), with registration code CEIFOD 0323 011, approved in its fourth version on 2 August 2023 by the Research Ethics Committee of the Faculty of Sports Organization at the Autonomous University of Nuevo León (CEIFOD; see Supplementary Materials S4). Formal authorization was also obtained from Club Tigres, the institution collaborating in the intervention. All participants were treated respecting the principles established in the Declaration of Helsinki of the World Medical Assembly [113].

Any substantial modification to the protocol will be submitted for review and approval to the ethics committee, and prior notification will be given both to Club Tigres and to the participants.

To ensure voluntary and ethical participation in the program, mandatory informed consent will be obtained, which will be explained and signed by the participants before their inclusion, in compliance with the committee’s guidelines. This process will be carried out by trained members of the research team, who will provide clear and understandable information about the study objectives, the participants’ role, the possible risks and benefits, and the option to withdraw from the study at any time without consequences.

In addition, strict measures will be implemented to protect data confidentiality: participants will be identified using alphanumeric codes, data will be stored in password-protected files and secure servers, and physical documentation will be kept in locked and closed locations. Only authorized personnel will have access to the information, and it will be ensured that the results are reported in aggregate, without identifying the individual participants.

## 3. Discussion

The present protocol outlines a psychoeducational intervention grounded in SDT, aimed at promoting physical activity and enhancing well-being in sedentary adults who are overweight, leveraging the social context generated by football clubs among their supporters as an incentive for participation.

The fact that the participants targeted in the protocol are football fans may introduce a certain behavioral bias [114,115], but it is consistent with the protocol’s framework theory, which is self-determination. Thus, at the beginning of the program, extrinsic reinforcement is needed to ensure—as far as possible—participant adherence [116]; however, once the program is established, the participants will evolve toward autonomy and self-determination, with the secondary objective of reducing the experimental mortality [117,118].

In addition, it is known that there are psychological dynamics in sports teams that help prevent dropout, such as normative and moderate group pressure [119] or increased cohesion [120].

Although it presents inherent methodological constraints, its implementation in both the face-to-face and semi-face-to-face modalities will allow for the analysis of potential changes and intervention-related effects, as well as the acceptability and contribution of each delivery format, and will explore whether the degree of the face-to-face interactions moderate the outcomes [121,122].

This analysis can help in recommending the applicability of the protocol in different areas, since one of the objectives is to provide a framework for the design, implementation, and evaluation of programs aimed at fostering health and well-being, and offers practical guidance to support application and adaptation across different contexts, leading to eventual future replication.

This study presents some important limitations, including the expected rate of participant attrition, which may create bias and reduce the representativeness of the sample, the absence of long-term follow-up, which limits the assessment of the sustainability of behavioral changes, and the use of evaluation instruments, as well as indicators such as burnout, derived from the sports context, whose applicability in sedentary overweight adults should still be considered with caution.

The integration of this protocol within a broader program that includes three interventions and a coach training component implies that observed changes in the study variables may be influenced by the effects of other interventions. While efforts will be made to isolate the specific impact of the present intervention, the results may reflect interactions among different program components, although this problem can also be mitigated to some extent by including it within the same theoretical framework of self-determination, since theoretical coherence could ensure that the strategies, language, and techniques used, as well as the objectives, are consistent, facilitating implementation, acceptance by the participants, and maximizing the potential results [123]. Finally, it should be noted that the results are limited in their generalizability due to the nature of the participants: all of them are football fans, as well as the difference in the “dose” of the intervention between the modalities, which could influence comparative outcomes.

Based on everything discussed and the limitations expressed, it seems clear that the most relevant future development is the empirical application of the protocol in the most efficient way possible, as well as presenting the results obtained, to be replicated for verification and eventual validation as a useful psychoeducational intervention to meet the stated objectives.

## 4. Conclusions

This article presents the PsicoFIT psychoeducational intervention protocol, grounded in Self-Determination Theory, which aims to promote healthy lifestyles and psychological well-being among overweight sedentary adults who are fans of a football club. The detailed description of its theoretical foundation, structure, implementation, and evaluation plan seeks to provide methodological guidance for the development of future interventions integrating psychological and behavioral approaches in sport-related contexts. The future empirical implementation of this protocol will allow for the analysis of its effectiveness, the psychological mechanisms involved, and the usefulness of its different delivery modalities.

